### Ethical approval

The study is approved by the Internal Review Boards of the American University of Beirut and Al-Sahel General Hospital. All participant pregnant women and support mothers will be requested to give their written informed consent prior to any study procedure. To secure confidentiality, all identifying information of participants, including name, medical and contact information as well as all collected data will be kept in a password protected computer that is kept secure in a locked cabinet by the principal investigator. Data access will be limited to the principal investigators and project coordinator working directly on the study.

To ensure appropriate medical and /or psychiatric care is provided to those mothers who need it, an ongoing evaluation process will take place with referral to appropriate services after physician notification and evaluation.

SM training will emphasize empathy and encouragement in order to ensure that breastfeeding mothers do not feel pressured to continue breastfeeding if they do not wish to do so. BFMis who fail to continue exclusive breastfeeding will continue to receive positive messages and get support if they so wish. This will continue until six months postpartum or until the BFMi decides to stop, whichever comes first. Mothers in the control group will receive the breastfeeding pamphlet and video upon exiting the study.

### Associated studies

1. Sub-study 1: The mother-to-mother breastfeeding support pilot study.

2. Sub-study 2: Development and validation of the Arabic breastfeeding knowledge, attitude and behavior (B-KAB) questionnaire.

3. Sub-study 3: Assessment of the impact of the complex breastfeeding intervention on knowledge and attitudes of breastfeeding mothers and their families.

4. Sub-study 4: A qualitative study on the experiences of breastfeeding mothers and support mothers participating in the complex breastfeeding promotion and support intervention trial.

5. Sub-study 5: Professional nurses experiences and satisfaction with the breastfeeding promotion and support intervention.

6. Sub-study 6: Impact of the complex breastfeeding intervention on the quality of life of participating mothers.

7. Sub-study 7: Cost-benefit and cost-effectiveness analyses of the complex breastfeeding intervention.

8. Sub-study 8: Development and validation of the Arabic Postpartum Quality of Life Questionnaire.

## Discussion

This study aims at investigating whether a complex intervention targeting new mothers’ breastfeeding knowledge, skills and social support within a Social Network and Social Support theory framework will increase exclusive breastfeeding rate and duration among women in Lebanon. We anticipate that the proposed multi-dimensional intervention will increase the low breastfeeding rates in Lebanon as it addresses previously identified barriers to successful breastfeeding in this country, namely inadequate maternal skills and self-efficacy, cultural misconceptions about breastfeeding, and lack of adequate social support. We believe that this unique multi-dimensional approach is a main strength of our study. Other strengths include the planned assessment of multiple outcomes over a five year period including quality of life, economic efficiency and maternal success in breastfeeding future babies, which have not been previously assessed in a clinical trial context.

The study may suffer from some limitations. The first limitation is the sampling frame which is the population of mothers who intend to breastfeed rather than all the population of expectant mothers. This frame was chosen because inclusion of women who do not intend to breastfeed will necessitate a much larger sample size, with further inflation of the budget thus making the study unfeasible. This selection bias however may exaggerate the difference in the 6-month exclusivity rates between the control and intervention groups. Another limitation is the single-blind design which is due to the difficulty in concealing the intervention from the research team members who will be directly involved in delivering the different aspects of the breastfeeding support package. However, this bias is unlikely to affect the main outcome of the study, the 6-month exclusivity rate, because of its objective nature.

The proposed complex intervention, if proven to be effective, will have a significant impact on infant morbidity and mortality, as well as maternal health and quality of life. Moreover, the study is expected to generate useful data that will encourage replication of the model in Lebanon as well as in similar developing countries. This study will highlight the compounding effect of using multiple methods to support breastfeeding mothers by utilizing the social network to promote exclusive breastfeeding.

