## Methods/Design

### Study design

A randomized controlled single-blind parallel-arm clinical trial to investigate whether a complex intervention targeting new mothers’ breastfeeding knowledge, skills and social support within a Social Network and Social Support theory framework will increase exclusive breastfeeding duration among women in Lebanon.

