### Outcome measures

#### Main outcome measure

The primary outcome is the percent difference in 6-month breastfeeding exclusivity rates between the intervention and control groups.

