### Data collection

#### Participant mothers

1. *Baseline:* Age, socio-economic status, education, employment status, mother’s religion, baseline breastfeeding knowledge and attitude, parity, previous breastfeeding, baseline social support, study site, residence.

2. *Month 1:* Baby’s gender, mode of delivery, pediatrician’s gender, first feed at hospital, rooming in, breastfeeding status, baby’s illness visits (number, diagnosis, money spent on medicine and doctor’s fees), baby’s hospitalizations (number, diagnosis, cost), days lost from work due to baby’s illness, days lost from work due to mother’s illness, cost of formula feeds/week, cost of water used to prepare formula/week, mother’s non-routine doctor visits due to breastfeeding, cost of infant food/week, QoL.

3. *Month 3:* Breastfeeding status, baby’s illness visits (number, diagnosis, money spent on medicine and doctor’s fees), baby’s hospitalizations (number, diagnosis, cost), days lost from work due to baby’s illness, days lost from work due to mother’s illness, cost of formula feeds/week, cost of water used to prepare formula/week, mother’s non-routine doctor visits due to breastfeeding, cost of infant food/week, QoL.

4. *Month 6:* Breastfeeding status, baby’s illness visits (number, diagnosis, money spent on medicine and doctor’s fees), baby’s hospitalizations (number, diagnosis, cost), days lost from work due to baby’s illness, days lost from work due to mother’s illness, cost of formula feeds/week, cost of water used to prepare formula/week, mother’s non-routine doctor visits due to breastfeeding, cost of infant food/week, QoL, satisfaction of mother with mother-to-mother support system, breastfeeding knowledge and attitude of mother, in-depth interviews with BFMis.

5. *Year 1:* Breastfeeding status, baby’s illness visits (number, diagnosis, money spent on medicine and doctor’s fees), baby’s hospitalizations (number, diagnosis, cost), days lost from work due to baby’s illness, days lost from work due to mother’s illness, cost of formula feeds/week, cost of water used to prepare formula/week, mother’s non-routine doctor visits due to breastfeeding, cost of infant food/week.

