#### Process evaluation

During the support period, an ongoing evaluation process will take place in order to identify potential problems and implement changes accordingly. The process evaluation will ensure that the intervention is delivered and implemented as planned by evaluating the dose delivered, dose received, and reached.

The study research assistant will contact BFMis and SMs bi-weekly to inquire about the support process, including address potential complaints. The inquiry findings will be shared with the principal investigator within one business day. Process amendments and/or improvements will take place within the same week if necessary. In case of a perceived need for referral by SMs, physician members of the research team will be notified within the same day and will contact the BFMi-SM pair in question to evaluate and confirm the medical urgency and refer-or not- accordingly. At the end of the support period, all records are returned to the research team. When the latter receives the records, a post-support survey is sent to the breastfeeding mother to fill and return for data entry and analysis. Separate surveys will be sent to each support mother and to the professional nurses to assess their satisfaction. All BFMis will be contacted by the research team on yearly basis for 5 years after the trial ends to ask about their success in breastfeeding future babies. In addition, all mothers in the control group will be contacted by the research team at 1 month, 3 months and 6 months after delivery for data collection and outcome assessment similar to the intervention group. They will also be contacted on yearly basis for 5 years after the trial ends to ask about their success in breastfeeding future babies.

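### The protocol dismisses bias from lack of blinding by calling 6-month exclusivity objective, but the only source it describes is what mothers who know their arm tell the research team

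*Protocol article*

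**What the plan says.** Main outcome measure: "The primary outcome is the percent difference in 6-month breastfeeding exclusivity rates between the intervention and control groups".

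Study design labels the trial "A randomized controlled single-blind parallel-arm clinical trial" and does not say who is blind. The Discussion lists the single-blind design as a limitation, citing the "difficulty in concealing the intervention from the research team members who will be directly involved in delivering" the support. It then sets the limitation aside: "this bias is unlikely to affect the main outcome of the study, the 6-month exclusivity rate, because of its objective nature".

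Under Data collection (Participant mothers), breastfeeding status is one of the items gathered about each mother at months 1, 3 and 6. The same visits record "cost of formula feeds/week, cost of water used to prepare formula/week", and also weekly spending on infant food. Process evaluation says control mothers "will be contacted by the research team at 1 month, 3 months and 6 months after delivery for data collection and outcome assessment", in the same manner as the intervention arm.

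Process evaluation also says: "The study research assistant will contact BFMis and SMs bi-weekly to inquire about the support process". By the protocol's own abbreviation, BFMis are breastfeeding mothers in the intervention group, so this contact has no counterpart among controls.

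**The concern.** Whether a baby has had only breast milk is seen by the family at home. No weighing, record check or other independent source is described, so the endpoint appears to be the mother's answer. The limitation paragraph considers only whether those delivering the support know the arm. It does not consider whether the mother does, although she supplies the data.

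She must know it. The intervention consists of classes closed to controls, a pamphlet and video, daily lactation visits in hospital, repeated home visits, a hotline and a support mother. A mother who has had months of encouragement towards exclusive feeding has more reason than a control to say she is still exclusive. That error favours the hypothesis. With an expected control rate of 2%, few such answers are needed to change the result of the test, and the text tells readers that the risk is small.

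**Working it through.** **Inputs.** Sample size section: control rate 2%, intervention rate 12%, 90% power, 5% type I error, 155 per group, 30% loss, 443 in total. Statistical methods: chi-square test for categorical variables, with no statement on continuity correction. Background: other reported 6-month rates of 4.1% to 10.1%. The over-reporting share f is an assumption, because the documents give no figure.

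**The plan's own figure.** The two-sided pooled formula for 2% versus 12% is n = [1.96·√(2·0.07·0.93) + 1.2816·√(0.02·0.98 + 0.12·0.88)]² / 0.10² = 134.7. The continuity correction is (n/4)·[1 + √(1 + 4/(n·0.10))]² = 154.1, rounded up to 155 per group. Inflating for loss gives 310/0.7 = 442.9, so 443. Both figures reproduce. Without the correction n would be 135, so the stated 155 implies a corrected calculation.

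**How few answers matter.** The expected control count is 155 × 0.02 = 3.1, so take 3 of 155.
- Without correction, 9 of 155 in the intervention arm gives p = 0.077 and 10 of 155 gives p = 0.047.
- With correction, 11 of 155 gives p = 0.056 and 12 of 155 gives p = 0.034.

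Starting from 3 in each arm, 7 over-reporting mothers (uncorrected) or 9 (corrected) reach significance with no true effect.

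**Chance of a significant result with no true effect.** If the true rate p is equal in both arms and a share f of non-exclusive mothers report exclusivity, the observed rate is p + (1 − p)·f. For p = 2% and f = 5% this is 0.02 + 0.98 × 0.05 = 6.9%. Rejection probabilities come from exact binomial enumeration of the two-sided 5% chi-square test with 155 per arm. At p = 2%:

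| f, intervention | f, control | Observed rates | Uncorrected | Corrected |
|---|---|---|---|---|
| 0% | 0% | 2.0% vs 2.0% | 4.5% | 1.2% |
| 2% | 0% | 4.0% vs 2.0% | 16% | 9% |
| 3% | 0% | 4.9% vs 2.0% | 28% | 18% |
| 5% | 0% | 6.9% vs 2.0% | 57% | 45% |
| 8% | 0% | 9.8% vs 2.0% | 87% | 80% |
| 5% | 2% | 6.9% vs 4.0% | 20% | 14% |
| 5% | 3% | 6.9% vs 4.9% | 11% | 7% |
| 8% | 3% | 9.8% vs 4.9% | 37% | 30% |

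**Other base rates.** With f = 5% in the intervention arm only, the uncorrected test rejects 40% of the time at a true rate of 4.1% and 23% at 10.1%.

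**Over-reporting that mimics the whole planned effect.** f = (0.12 − 0.02)/(1 − 0.02) = 10.2%, or 155 × 0.10 = 15.5 mothers.

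**The case against.** The strongest reply is that the calculation puts all the error in one arm. Controls also intended to breastfeed, consented to the same trial and are asked on the same schedule, so some of them will over-report too. This stands: 2% over-reporting among controls cuts 57% to 20%. Only the difference between arms does the harm. The share itself is assumed, and the more alarming values of f should not be read as expected.

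The protocol also contains some protection. Under Ethical approval, support mothers are trained so that women do not feel pressed to continue, and women who stop exclusive feeding still receive positive messages. Monthly home visits and support mothers' logs make some false answers checkable. This weakens the incentive to over-report, but none of it is tied to how the outcome is ascertained.

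A reader might infer that the outcome interviewers are stated to be unblinded. They are not. The Discussion says that those delivering support cannot be blind, and Process evaluation says the research team makes the outcome contacts. Whether these are the same people is not stated. Similarly, the bi-weekly contact is an enquiry about the support process and not itself support. The silence on who is blind does not prove the single-blind label false, since a condensed article may leave that to the full protocol. None of this makes the mother blind or her answer objective.

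**Conclusion.** The point holds as an unsupported statement about the primary outcome. The protocol gives objectivity as its reason for discounting the bias, yet describes only an outcome obtained by asking mothers, and those in one arm must know what they received. That the data are mother-reported is an inference, but no other source is named.

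On the plan's 2% base rate, over-reporting of 2% to 8% confined to the intervention arm raises the chance of a false positive to between 16% and 87% (uncorrected). Continuity correction, over-reporting in controls and a higher base rate each reduce this.

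Two stronger readings are tempting and not supported. The first is that the protocol claims the outcome is immune to unblinding; it says only that an effect is unlikely. The second is that a few points of over-reporting equal the target effect. At 5% the spurious difference is 6.9% − 2.0% = 4.9 points, about half of the planned 10. The whole contrast needs about 10%.

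**What to change.** 1. In the Discussion, delete the argument from objectivity and list differential self-report as a limitation on the primary conclusion.
2. State who is blind, or drop the single-blind label.
3. Keep the primary outcome as defined. Add a pre-specified sensitivity analysis that reclassifies as non-exclusive any mother who reports exclusivity but whose formula, formula-water or infant-food cost records contradict it. These items are already collected in both arms at months 1, 3 and 6.
4. Within existing staff, have the breastfeeding-status questions asked by someone who neither delivers support nor makes that mother's bi-weekly process calls. Ask them before the month-6 satisfaction items, which reveal the arm.

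The cost is protocol wording, one derivation rule, the order of questions and some allocation of tasks. No new data item is needed and the sample size is unchanged. There are two small downsides. The cost items are also mother-reported, so the check reduces the bias without removing it. It may also misclassify a few mothers who have just started solids at month 6, which is why it belongs in a sensitivity analysis and not in the primary definition.

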## Appendix-A

### Antenatal breastfeeding education class

**Purpose:** To promote breastfeeding among expectant mothers and improve their breastfeeding-related knowledge and skills.

**Description:** A one-hour session of educational activities that aim at promoting breastfeeding among expectant mothers and their families.

### Objectives

At the end of the session the expectant mother will be able to:

1. Identify the importance of breastfeeding to mother and baby

2. Know the mechanism of milk production

3. Practice adequate breastfeeding technique, including recognize different breastfeeding positions and proper latch

4. Understand the concept of rooming in and its benefits

5. Adapt the concept of breastfeeding maintenance after return to work

6. Identify concerns related to breastfeeding and how to overcome them

### Course content

1. Why is breastfeeding important

2. Benefits of breastfeeding to mother and baby

3. Common breastfeeding myths

4. How does breastfeeding work (anatomy and physiology of milk production)

5. Baby’s readiness to eat

6. Techniques of a good latch

7. Different positions during breastfeeding

8. Breast care

9. Preventing soreness and engorgement

10. Rooming-in to promote breastfeeding

11. Working mothers and breastfeeding

12. Family support during breastfeeding

13. Common concerns related to breastfeeding

### Course material

1. Power point presentation

2. Handouts

3. Demonstration

### Teaching aids

1. Doll

2. Breast Model

3. Others if needed

### Teaching formats

1. Interactive discussion

2. Case study

3. Pre- and Post- Assessment checklist

4. Role play

## Abbreviations

SSPS: Statistical package for social sciences; MENA: Middle East and North Africa; AUBMC: American University of Beirut Medical Center; SGH: Sahel General Hospital; KAB: Knowledge-Attitude-Behavior; IIFAS: Iowa infant feeding attitude scale; IFI: infant feeding intention scale; BBQ: Breastfeeding behavior questionnaire; SM: Support mother; BFMi: Breastfeeding mother in intervention group; QoL: Quality of life; WHO: World Health Organization; UNICEF: United Nations International Children’s Emergency Fund; LOVE: Listen observe validate empower/educate.
